#### 8.9. Annual reports to the Specified Authorized Committee for Regenerative Medicine and the Minister of Health, Labour and Welfare

- 1) The hospital director shall report to the Specified Authorized Regenerative Medicine Committee on the following items annually, starting from the date of submission of the plan for the provision of regenerative medicine to the Minister of Health, Labour and Welfare, within 90 days after the expiration of the designated period.
  - Number of subjects who have received this regenerative medical treatment
  - The occurrence and progress of diseases, etc. related to this regenerative medical treatment
  - Evaluation of the safety and scientific validity of this regenerative medicine
  - Matters concerning involvement in this regenerative medicine, etc. as prescribed in each item of Article 8-8(1) on the Act on the Safety of Regenerative Medicine (ASRM)
  - Status of occurrence of noncompliance to this Ministerial Ordinance or the plan for providing regenerative

medicine, and subsequent actions taken

- 2) After hearing opinions from the Specified Authorized Regenerative Medicine Committee, the hospital director shall report to the Minister of Health, Labour and Welfare on the following items annually, starting from the date of submission of the plan for provision of regenerative medicine within 90 days after the expiration of designated period.
  - Name of the Specified Authorized Regenerative Medicine Committee
  - Opinion of the Specified Authorized Regenerative Medicine Committee, on the appropriateness of continuation of this study.
  - Number of subjects who have received this regenerative medical treatment

#### 8.10. Report of Serious Incidents to the Minister of Health, Labor and Welfare

- 1) In the event of a situation that may have a significant impact on ensuring the safety of the specified cellular processed products (a serious incident), the specified cellular processed product manufacturer must take the necessary measures and promptly report to the study site (Chiba University Hospital) and the Minister of Health, Labour and Welfare.
- 2) When storing Specified Cellular Processed Products in which a serious incident has occurred, the Specified Cellular Processed Products must be classified and stored for a certain period of time, and then properly processed.

#### 8.11. Management of incompliance issue

When the Hospital Director or the PI becomes aware that the study is not in compliance with the Act on the Safety of Regenerative Medicine (ASRM) or the Regenerative Medicine Provision Plan, he/she shall promptly report to the Hospital Director to that effect.

In addition, when a particularly serious incompliance issue is found, the Hospital Director or the PI shall promptly obtain the opinion of the Specified Authorized Committee for Regenerative Medicine.

### 9. Endpoints

#### 9.1. Primary endpoint

Dose Limiting Toxicity (DLT)

##### **【Rationale】**

The primary purpose of this study is to evaluate the tolerability of the combination therapy of DC/Gal and iPS-NKT cells, based on the DLT expression rate, which is a typical endpoint in Phase I studies of drugs.

## 9.2. Secondary endpoints

### 【Efficacy】

- Response rate (RECIST ver.1.1)
- Disease control rate (Subjects reached on CR, PR, or SD based on RECIST ver.1.1)

### 【Safety】

- Adverse event (Type, frequency, and severity)
- Changes in Laboratory Values

#### 【Rationale on secondary efficacy endpoints】

Since this is an FIH study of DC/Gal and iPS-NKT cell combination therapy for malignant tumors, the evaluation of efficacy was set as a secondary endpoint.

#### 【Rationale on secondary safety endpoints】

Secondary safety endpoints are established to evaluate in as much detail as possible all adverse events that occurred in this study, in addition to the DLT evaluation.

## 9.3. Exploratory endpoints

- Remaining iPS-NKT cells in peripheral blood at 1 week after iPS-NKT cell administration
- Dynamics measurement (iPS-NKT cell concentration in peripheral blood on day 7 after iPS-NKT cell administration)
- Tumor immunokinetic analysis

#### 【Rationale】

The exploratory endpoints were established to elucidate the mechanism of action of iPS-NKT cells in the human body and the effects of iPS-NKT cells on the immunokinetic and function of the subject.

## 9.4. Exploratory Immunological evaluation

The following immunological analyses will be performed using blood samples for immunological testing.

- Immune cell repertoire analysis
- Omics analysis (including genetic testing) in peripheral blood immune cells

Omics analysis in peripheral blood immune cells ("Omics analysis") will be performed to explore the molecular biological effects of iPS-NKT cells on the differentiation and function of peripheral blood immune cells when administered into the tumor-trophoblastic artery of head and neck cancer patients.

Omics analysis will be performed using residual blood samples (approximately 12 mL) collected for pharmacokinetic and immune cell repertoire analysis of peripheral blood after obtaining consent for the Omics analysis from each subject. When analyzing the specimens, personal identifiable information will be deleted, new IDs will be assigned, and the specimens will be anonymized, and analyzed at Chiba University and RIKEN, as necessary. The genetic information revealed by the analysis will not be disclosed to the subjects in principle, since the usefulness of the genetic information is not clear at the time the research is initiated. However, genetic information may be disclosed after deliberation by the Bioethics Review Committee if the usefulness of the genetic information becomes clear, or if a relationship to other serious diseases is discovered by chance, and after considering the wishes and benefits of the subject and their relatives. The handling of samples and data shall be in accordance with "16.1. Storage of Samples" and "16.2. Disposal of Specimens."

## 10. Statistical Considerations

The statistical analysis plan for this study is summarized below. The details of the statistical analysis plan are described in the statistical analysis plan. The outline of this study plan may be revised in the statistical analysis plan if the definition of the primary endpoints or the analysis methods are changed.

### 10.1. Population to be analyzed

#### 10.1.1. Safety analysis population and DLT evaluation population

Subjects those who registered in the study and treated with the auto-DC/Gal will be the target population for safety analysis. However, cases of non-compliance with the Regenerative Medicine Act will be excluded from the safety analysis population. Of the safety analysis population, all subjects who could not be appropriately evaluated during the DLT evaluation period for reasons other than the auto-DC/Gal or the iPS-NKT cell-related toxicity will be excluded from the DLT evaluation population. In the event that a subject is excluded from the analysis, a new subject will be added to the cohort.

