## 5. Study Method

### 5.1. Design

This is an open-label, single arm, Phase I study to evaluate the tolerability, safety, pharmacokinetics, pharmacodynamics, and antitumor effects of iPS-NKT cell in combination with auto-DC/Gal in patients with recurrent or advanced head and neck cancer who are refractory or intolerant to standard of therapy.

The dosing regimen involves both a submucosal injection of auto-DC/Gal at  $1.0 \times 10^8$  cells (fixed dose) followed by tumor-feeding arterial administration of the iPS-NKT cell at one of two dose levels: initial dose (first dose) cohort:  $3.0 \times 10^7$  cells/ $m^2$ , or second dose cohort:  $1.0 \times 10^8$  cells/ $m^2$ , administered at once, respectively. The iPS-NKT cell is administered at once five days after the DC/Gal injection. We avoid same-day administration of the investigational product to more than two subjects, and there must be a minimum interval of at least seven days before administering the investigational product to the following subject. We employed the three-by-three (3+3) design for dose escalation in this trial. Ultimately, the maximum tolerated dose (MTD) will be determined based on a total of six subjects with one or less DLT occurrences.

The screening period begins after obtaining the informed consent from each subjects. Based on the results of the screening tests, eligible subjects are registered in this study. One week prior to the start of study treatment, the subject's peripheral blood is collected, and auto-DC/Gal is manufactured (auto-DC/Gal preparation period).

DLT assessment period starts from the injection of auto-DC/Gal to 14 days after the iPS-NKT cell administration. During DLT assessment period, subjects will be carefully monitored under hospitalization. The PI or SI may leave the hospital at his/her own discretion only if the patient does not develop non-hematologic toxicity or hematologic toxicity of Grade 2 or higher and Grade 3 or higher on or after Day 7 of iPS-NKT cell administration, and be able to contact the study site and home doctor of the subjects, if any, in the event of an adverse event.

The Independent Data Monitoring Committee, consisting of members designated by the PI and study coordinating physicians, monitors the safety of the study and may make recommendations regarding the continuation of the study.

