## 5.2. Dose Limiting Toxicity (DLT)

DLT is defined as the following adverse events observed during the DLT assessment period, in which a causal relationship with auto-DC/Gal or iPS-NKT cell cannot be denied. Grading is determined according to the CTCAE ver.5.0 translated in Japanese by the Japan Clinical Oncology Group (JCOG).

- 1) Grade 4 or higher hematological toxicities
- 2) any non-disease-related blood toxicity requiring any transfusion or granulocyte-colony stimulating factor (G-CSF) administration
- 3) grade 3 or higher non-hematological toxicities (excluding transient clinical laboratory abnormalities, diarrhea, nausea, vomiting, or other manageable systemic symptoms that recovered to grade 2 or below under appropriate treatments)
- 4) AEs lead to blood transfusion.

If the PI suspects the occurrence of DLTs, the PI can consult the Independent Data Monitoring Committee (IDMC), and the IDMC determines the continuation or termination for the patient. Subjects who do not complete the DLT assessment period for reasons other than DLT will not be considered DLT evaluable cases and then another

subject will be supplemented in the same dose cohort.

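### Section 10.1.1 lets a treated subject with a DLT drop out of the reported DLT rate and safety tables, and its evaluability rule conflicts with 5.2

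*Protocol*

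**What the plan says.** Protocol 10.1.1 sets the base of the safety population: "Subjects those who registered in the study and treated with the auto-DC/Gal will be the target population for safety analysis". The next sentence narrows it: "cases of non-compliance with the Regenerative Medicine Act will be excluded from the safety analysis population". The DLT population is a subset of that reduced set. It leaves out "all subjects who could not be appropriately evaluated during the DLT evaluation period for reasons other than the auto-DC/Gal or the iPS-NKT cell-related toxicity". The section ends: "In the event that a subject is excluded from the analysis, a new subject will be added to the cohort". Nothing in it protects a subject who was exposed, or who had a DLT, from the compliance exclusion.

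Under 10.5 and 10.5.2.1, the DLT count, percentage and confidence interval per dose are computed in the DLT population. Under 10.5, the secondary safety analyses are run in the safety population.

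Section 5.2 has its own evaluability rule: "Subjects who do not complete the DLT assessment period for reasons other than DLT will not be considered DLT evaluable cases". Such a subject is replaced within the same dose cohort.

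Other sections count differently. The synopsis and 13.1 base the stopping rule on patients or subjects with a DLT, not on members of an analysis set. Section 10.6 gives the IDMC the final DLT judgement and has it decide on all safety information.

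**The concern.** There are two separate defects.

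First, compliance with the Act is a legal status. What happened to a person who received the cells is evidence about the product whatever that status is. As written, one compliance ruling takes a treated subject out of the safety tables, out of the DLT population and so out of the primary rate. The trial is open-label, 10.3 leaves case handling to the coordinating physician and the statistical analyst, and no text requires the ruling to be made before toxicity is known. With at most six analysed subjects per dose, one subject moves the reported result materially.

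Second, 5.2 and 10.1.1 disagree about a subject who stops because of a product-related toxicity that falls short of a DLT. If one section steers replacement and the other the analysis, escalation and the reported rate can rest on different subjects.

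**Working it through.** **Inputs.** 3+3 design with two doses; stop at two or more DLTs, tolerable at one or fewer of six (synopsis, 1.3.3). At most 12 analysed, six per dose, and a minimum of 2 (10.2). Population rules from 10.1.1 and 5.2; primary analysis from 10.5.2.1. The plan names no interval method, so I assume exact (Clopper-Pearson) limits. The events in the examples are also assumed.

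**Step 1, the plan's own figure.** Maximum 2 doses × 6 = 12; minimum 2, from two consecutive DLTs. The stated 2 to 12 is reproduced. It is not affected by this point, because the 12 are patients analysed.

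**Step 2, the compliance exclusion.** Suppose two of six treated subjects at a dose have a DLT and one of those two is ruled a non-compliant case. For x events in n, the lower limit is the 2.5% quantile of Beta(x, n−x+1) and the upper limit the 97.5% quantile of Beta(x+1, n−x).

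| Reported set | Rate | 95% CI |
|---|---|---|
| All treated subjects kept | 2/6 = 33.3% | 4.3-77.7% |
| One DLT subject excluded, replacement has no DLT | 1/6 = 16.7% | 0.4-64.1% |
| One DLT subject excluded, no replacement enrolled because the study has stopped | 1/5 = 20.0% | 0.5-71.6% |

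Both alternatives follow 10.1.1 to the letter and report one DLT where two occurred. The excluded subject's adverse events also leave the safety tables.

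**Step 3, 5.2 against 10.1.1.** The protocol's own rules produce the conflicting case. Take a related Grade 3 hematological toxicity after auto-DC/Gal that does not recover before iPS-NKT and needs no transfusion or G-CSF. Treatment is discontinued (5.9.1, item 1), but the event is not a DLT, because criterion 1 in 5.2 starts at Grade 4. By 5.1, "DLT assessment period starts from the injection of auto-DC/Gal to 14 days after the iPS-NKT cell administration". Without iPS-NKT that window cannot be completed.

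- Under 5.2 the reason is not a DLT, so the subject is non-evaluable and replaced.
- Under 10.1.1 only subjects not evaluable "for reasons other than the auto-DC/Gal or the iPS-NKT cell-related toxicity will be excluded from the DLT evaluation population". This reason is related toxicity, so the subject stays and is not replaced.

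For one cohort of six with one such withdrawal, and one DLT among the other subjects:

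| Rule for replacement | Rule for analysis | Treated | Analysed | Withdrawal counted? | Reported rate |
|---|---|---|---|---|---|
| 5.2 | 5.2 | 7 | 6 | No | 1/6 = 16.7% |
| 10.1.1 | 10.1.1 | 6 | 6 | Yes | 1/6 = 16.7% |
| 5.2 | 10.1.1 | 7 | 7 | Yes | 1/7 = 14.3% |
| 10.1.1 | 5.2 | 6 | 5 | No | 1/5 = 20.0% |

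Applied consistently, either rule gives six analysed, but not the same six. Seven arises only if 5.2 governs replacement and 10.1.1 governs analysis, and it would exceed the six per dose in 10.2. In every row the adjudicated DLT is still counted.

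**The case against.** **The dose decision has its own safeguards.** A reader might infer that dropping one DLT turns a stop into a tolerable dose. The protocol does not support that. The synopsis and 13.1 count patients or subjects with a DLT, suspected DLTs go to the IDMC at once (7.1.3.2), and the IDMC decides on all safety information (10.6). The statistical analysis comes only after administration is complete and data are fixed (10.5). Nothing says an adjudicated DLT is erased from the stopping count. For the same reason I do not rely on operating characteristics. With q = 1−p, the chance of declaring a dose tolerable is q³ + 3pq²·q³, which is 0.494 at a true DLT rate p of 0.30. Always removing and replacing the first DLT would raise it to 0.742. That assumes both that the excluded case is always a DLT and that the analysis set drives the decision, and the text supports neither. This objection stands and limits the point to reporting and replacement. The safeguard is not complete: item 3 of 13.1 names only the first dose, so the second relies on the synopsis wording and the IDMC.

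**The criterion is legal, not outcome-based.** It could equally remove a subject without a DLT, and no timing is given, so a systematic bias toward tolerability is not shown. That is fair. It does not answer the case in which the excluded subject did have toxicity, which the report would then omit.

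**The law may bar some data.** That may be what 10.1.1 intends; 10.1.2 names failure to obtain consent as a serious violation. But 10.1.1 excludes every non-compliant case without that limit, and 8.11 sets out reporting of non-compliance without defining which cases lose their data.

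**Adverse events are still reported individually** (8.4, 8.8). True, but the primary rate and the summary tables would not show them.

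**The statistical analysis plan may clarify.** It is not shown, but both rules are fixed in this protocol, and replacement operates during the trial, before any analysis.

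**Conclusion.** The point holds for the reported DLT rate, the safety tables and cohort replacement. Followed as written, 10.1.1 can leave out an observed toxicity in an exposed subject, for example 2/6 reported as 1/6, and the report can then disagree with the subject-based stopping count and with what the IDMC reviewed. The size rests on one assumed excluded DLT; the protocol gives no expected frequency of non-compliance, so no probability can be attached.

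The conflict between 5.2 and 10.1.1 is real for early withdrawal due to related toxicity that is not a DLT. It changes who is replaced and who is analysed, but it does not remove a DLT, and it should not be read as adding to the first defect.

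**What to change.** 1. Define the safety population as all subjects who received any auto-DC/Gal or iPS-NKT cells.
2. Flag cases of non-compliance with the Act, present the safety results with and without them, and exclude data only where their use is legally barred.
3. State that every IDMC-adjudicated DLT counts in the primary analysis whatever the subject's compliance status.
4. Reconcile 5.2 and 10.1.1 into one DLT-evaluable definition, worded identically in both places and used for both replacement and analysis. It should say explicitly how a related, non-DLT early withdrawal is handled. The replacement sentence in 10.1.1, "In the event that a subject is excluded from the analysis, a new subject will be added to the cohort", should refer to that definition only.

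The cost is a wording amendment and one extra sensitivity table. The reported DLT rate may be slightly less favourable. The sample size range does not change.

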#### 10.1.2. Largest analyzed population (full analysis set : FAS)

All subjects those who registered in the study and have received at least one dose of the auto-DC/Gal or the iPS-NKT cells and for whom efficacy data are available will be the Full Analysis Set (FAS). However, subjects for whom baseline data were not obtained and subjects with serious violations of the study protocol (e.g., failure to obtain consent) will be excluded.

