### 5.9.2. Study discontinuation

If any of the following criteria are met, the PI or SI will discontinue the study in the subject.

- 1) When progression of the primary disease requiring concomitant use of prohibited drugs or concomitant therapy is recognized, as judged by the PI or SI.
- 2) When the subject requests discontinuation of the study.
- 3) When a subject is found to be ineligible after his/her registration.
- 4) Other cases in which the PI or SI determines that the subject is unable to receive DC/Gal.

When a subject who meets the criteria for discontinuation is identified after the start of DC/Gal or iPS-NKT cell administration, the PI or SI should explain this to the subject, discontinue the study, and take appropriate measures.

In the case of discontinuation due to adverse events (including abnormal changes in laboratory test values), necessary examination and observation should be conducted until it is determined that the subject can be discharged or transferred to another hospital. For adverse events for which a causal relationship with DC/Gal or iPS-NKT cell cannot be denied, observation should be continued as much as possible until symptoms recover or become mild, in principle.

The PI or SI should record the date of discontinuation, reason for discontinuation, and other necessary information. In addition, the PI or SI should perform the stipulated items at the time of discontinuation as possible.

In the case of discontinuation, the "date of discontinuation" shall be the date when the PI or SI decides to discontinue the study, not the date when the event that is the reason for discontinuation occurs or becomes known.

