#### 7.1.3.3. Observation Period

On Days 1, 15, and 28 of the observation period, the following will be performed

- Body Weight
- ECOG PS
- Hematology
- Blood Biochemistry Test
- Urinalysis
- Pregnancy test (for women with childbearing potential only, on Day 28)
- Chest X-ray
- Adverse event evaluation
- Contrast-enhanced CT (or contrast-enhanced MRI) scan (tumor evaluation, on Day 15)
- Anti-HLA antibody test (only on Day 1)
- Immune cell repertoire analysis (only on Day 1)

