#### 7.1.3.4. Study Discontinuation

Within 7 days of the decision by the PI or SI to discontinue the study, the following will be performed as possible. However, if post-treatment is to be initiated, the following must be performed prior to the start of post-treatment.

- Body Weight
- ECOG PS
- Hematology
- Blood Biochemistry Test
- Urinalysis
- Pregnancy test (for women with childbearing potential only)
- Chest X-ray
- Adverse event evaluation
- Contrast-enhanced CT (or contrast-enhanced MRI) scan (tumor evaluation)
- Anti-HLA antibody test

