### 10.4. Data Handling

In principle, the handling of data during data tabulation and analysis shall be as follows. In case of doubt, the statistical expert and the study coordinating physician will discuss and decide before fixing the data. Missing values will not be supplemented.

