### 10.5. Statistical analysis items and analysis plan

Analysis will be performed after the auto-DC/Gal or the iPS-NKT cell administration is completed in all cases and data are fixed.

For the safety analysis, a frequency table will be created for each System Organ Class (SOC) and the Preferred Term (PT) in MedDRA/J for the occurrence of DLT in the DLT evaluation target population. In addition, the following analyses in the safety analysis target population will be conducted as secondary

evaluations.

For the efficacy evaluation, analyses will be performed on the Full Analysis Set (FAS) and on the analysis population consistent with the study protocol (PPS).

Details of the statistical analysis will be specified in a separate statistical analysis plan to be prepared prior to data fixation.

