#### 10.5.2.2. Secondary analysis

The following secondary endpoints will be analyzed for the purpose of providing supplementary discussion to the main analysis results. For the safety secondary endpoints, frequency tables will be created for all adverse events that occur after the auto-DC/Gal or the iPS-NKT cell administration for each the system organ class (SOC) and the preferred term (PT) in MedDRA/J. Similar frequency tables will be created by dose, severity, causal relationship to the auto-DC/Gal or the iPS-NKT cells, and the CTCAE Grade. Summary statistics will be calculated for Blood Biochemistry Test results. In addition, summary statistics of the difference between baseline and each time point will be calculated. A trend chart of laboratory values will also be created. For the efficacy secondary endpoints, the response rate and disease control rate based on RECIST v.1.1 evaluated by the PI or SI will be calculated, and the 95% confidence interval for these rates will also be calculated. Because this is an exploratory study, the P-values and confidence intervals for hypothesis testing obtained from statistical analysis are intended to identify and estimate meaningful variation and are not conclusive as to the presence or absence of efficacy. Other items and details are described in the statistical analysis plan.

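### The full analysis set drops treated subjects with no efficacy data, so those who die, are too ill or withdraw without any post-baseline scan leave the denominator of the response and disease control rates

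*Protocol*

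**What the plan says.** Section 10.1.2 defines the FAS as registered subjects who "have received at least one dose of the auto-DC/Gal or the iPS-NKT cells and for whom efficacy data are available". It also excludes subjects with no baseline data or with serious protocol violations. Section 10.4 adds: "Missing values will not be supplemented". Section 10.5 names the FAS and the per protocol set (PPS) as the only efficacy populations. Section 10.5.2.2 asks for the response rate and the disease control rate, "and the 95% confidence interval for these rates will also be calculated". Section 9.2 defines disease control as complete response, partial response or stable disease.

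The Study Calendar in Section 7.1 and Section 7.1.3.3 schedule one post-treatment CT or MRI, on Day 15 of the observation period. Sections 7.1.3.4 and 7.1.3.5 add imaging at discontinuation. For that visit, Section 7.1.3.4 says that within 7 days of the decision "the following will be performed as possible", and then makes the assessments mandatory if further treatment is to begin. Section 5.9.2 lists among the reasons for leaving the study: "When progression of the primary disease requiring concomitant use of prohibited drugs or concomitant therapy is recognized".

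No section says that a death, a not-evaluable result or an absent post-baseline scan counts as non-response or as lack of disease control.

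**The concern.** Membership of the main efficacy set depends on the outcome having been observed. In this population the reasons for having no scan (death, rapid decline, a move to supportive care) are closely tied to treatment failure. Removing such subjects takes failures out of the denominator and leaves the numerator unchanged, so both rates move upward.

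The two rates are the only clinical efficacy endpoints in a small uncontrolled study. No comparison arm would show the selection, and readers will set the figures beside those of the earlier cell-therapy studies summarised in Section 1.2.6.

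**Working it through.** **The plan's own figure.** Section 10.2 gives a maximum of 12, from 2 doses × 6 subjects = 12, which reproduces. The protocol states no expected response rate, disease control rate or dropout rate, so every count below is an assumption. The number treated could exceed 12, because Sections 5.2 and 10.1.1 replace subjects who cannot be assessed for dose-limiting toxicity.

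**Who is lost.**
- Progresses, stops the study and is scanned at discontinuation: has efficacy data, stays in the FAS and counts as progressive disease.
- Progresses and starts another therapy: the scan must come first (Section 7.1.3.4), so the subject also stays.
- Dies, is too ill, goes to supportive care only, or withdraws without any scan: nothing makes a scan binding, and if none exists the subject leaves the FAS.

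**Size of the shift.** Let N be the number treated, m the number with no post-baseline assessment, and x the number of successes. With every lost subject a failure, the all-treated rate is x/N and the FAS rate is x/(N-m), so the ratio is N/(N-m). The table takes N = 12, 6 with disease control and 2 responders, with exact (Clopper-Pearson) 95% intervals. The protocol names no interval method.

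| m | N/(N-m) | Disease control in FAS | Response in FAS |
|---|---|---|---|
| 0 | 1.00 | 6/12 = 50.0% (21.1 to 78.9) | 2/12 = 16.7% (2.1 to 48.4) |
| 1 | 12/11 = 1.09 | 6/11 = 54.5% (23.4 to 83.3) | 2/11 = 18.2% (2.3 to 51.8) |
| 2 | 12/10 = 1.20 | 6/10 = 60.0% (26.2 to 87.8) | 2/10 = 20.0% (2.5 to 55.6) |
| 3 | 12/9 = 1.33 | 6/9 = 66.7% (29.9 to 92.5) | 2/9 = 22.2% (2.8 to 60.0) |

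In a single cohort of six with 3 controlled, one lost subject moves disease control from 3/6 = 50% to 3/5 = 60%, and two lost move it to 3/4 = 75%.

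**Is a loss of 1 to 3 plausible?** The iPS-NKT cells follow DC/Gal by 5 days. A scan on observation Day 15, 28 days after the iPS-NKT cells, therefore falls 5 + 28 = 33 days after DC/Gal. Section 3.1 requires an expected prognosis of at least 3 months. The protocol gives no median survival for this population, so I assume exponential survival with medians of 3, 6 and 9 months. The chance of death by day d is 1 - 2^(-(d/30.4)/median).

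| Assumed median | Death by day 33 | Expected among 12 | Chance of at least one |
|---|---|---|---|
| 3 months | 22% | 2.7 | 95% |
| 6 months | 12% | 1.4 | 78% |
| 9 months | 8% | 1.0 | 63% |

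The scan date is itself inconsistent. Section 5.1 puts it 14 days after the iPS-NKT cells, which is 5 + 14 = 19 days after DC/Gal. Section 7.1.3.5 calls it the first day of the observation period but gives 28 days. At day 19 the expected deaths among 12 are 1.6, 0.8 and 0.6 for the same three medians.

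These counts are only a guide to m. Some subjects who die will already have had a discontinuation scan, and some survivors will have none.

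**The case against.** A reader might infer that everyone who progresses before the scheduled scan disappears from the denominator. The documents do not support that. Progression that needs prohibited therapy leads to discontinuation, imaging is planned at that point, and it is mandatory before further treatment. Subjects who only stop study treatment move to the observation period with testing continued (Section 5.9.1). This part of the objection stands and confines the problem to subjects with no post-baseline scan at all.

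It can also be said that efficacy data is an undefined term, that the RECIST appendix and the statistical analysis plan are not at hand, and that declining to impute does not forbid reporting a subject as not evaluable within the denominator. That is fair as far as it goes. The analysis plan may soften the rule. But the protocol states an explicit population definition that depends on the outcome being available, and nothing in the text shown reverses it.

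The direction of bias assumes that lost subjects are failures. For a withdrawal this need not hold. If one of the 6 controlled subjects withdrew unscanned, the FAS would give 5/11 = 45.5%, below 50%. This stands as a condition on the formula.

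Finally, three lost of 12 is at the high end, the intervals are wider than the shift, and Section 10.5.2.2 disclaims any conclusion on efficacy. All true, and these points lower the severity. They do not remove a bias built into the definition.

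**Conclusion.** The concern holds for treated subjects who have no post-baseline assessment of any kind. For them the FAS definition biases the response and disease control rates upward by N/(N-m), provided that they are failures. That is 1.09 to 1.33 for an assumed 1 to 3 of 12, or disease control of 55% to 67% where the all-treated figure is 50%. The PPS does not correct this, since Section 10.1.3 gives no rule for counting an absent outcome as a failure.

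Severity is moderate. A reader might infer that the trial's conclusions are at risk, but the documents do not support this. Both rates are secondary, with no threshold and no confirmatory test (Section 10.2). No escalation, stopping or maximum tolerated dose rule uses them. The primary analysis of dose-limiting toxicity is made in a different population. The counts and survival medians used here are assumptions.

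**What to change.** In Section 10.1.2, or in a dedicated definition for the two rates, take as denominator all subjects who received any study cells and had a baseline tumour assessment. State that death, a not-evaluable result or no post-baseline assessment counts as non-response and as lack of disease control. Add to Section 10.4 that this is a classification rule for these two endpoints, so that it does not conflict with the ban on filling in missing values. Keep the present FAS and the PPS as supportive analyses, and report the numbers treated and assessed side by side for each dose. Reconcile the scan date between Sections 5.1, 7.1.3.3 and 7.1.3.5, because it affects how many subjects can be lost.

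The cost is a change of wording in the protocol and matching text in the analysis plan, made before the data are fixed. No new data are needed. The reported rates may be lower, and a subject who withdraws unscanned while stable would be counted as a failure. The supportive FAS analysis would show how much that matters.
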